***Analysis of collected data***

**Descriptive analysis**

Qualitatives data will be described in frequency and percentage, quantitative data by mean (±SD)-type) if distribution is normal, or median (quartiles) in other cases.

**Main Analysis**

For the main criteria, 2 analysis will be performed:

- At a treatment group level
- At an individual level

Approximately 60% of included patients will have a temporary contra-indication to systemic heparinisation ranging from 3 to 6 sessions (1 to 2 weeks). These patients will not be analysed individually and will contribute to the global principal analysis.

The global principal analysis will be performed according to 2 approches (MG Kenward and B Jones, The analysis of binary and categorical data from crossover trials, Statistical Methods in Medical Research, 1994 :325-344) :

- a marginal model estimating the effet of treatments taking into account other covariates (order effect or group effect, the Generalized Estimating Equations)
- a subject-specific model using a latent variable taking into account independent responses for a given subject réponses indépendantes pour un sujet. This model is also suited to low numbers of patients.

In the putatively 40% of patients (25 to 30 patients) that may have a prolonged contra-indication to heparin, anb individualized analysis will be performed (after at least 18 sessions to warrant sufficient power). Below 18 sessions, patients will only contribute to the global analysis, as described above.

For the individual analysis, The percentage of technical failures (technique A vs B, and also technique A vs C) will be performed. The exact Fisher test in this setting may be viewed as a randomisation test (ES Edington, Statistics and single case analysis, Progress in behavior modification. Academic Press, Inc. 1984;vol 16 :83-119). Appairment will not be taken into account. This is possible since the dialysis sessions and the efferent judgement criteria are statitically independent. Significativity threshold will be of 10% for a bilateral test, justified by the impoortance given to clinical significance (ES Edington).

At the end of this analysis:

- if one or several techniques are efficient, the patient will end the study
- if no technique apperas superior, the patient may continue the study for at least one triplet of sessions.

To avoid multiple analysis and alpha risk, a new analysis will be performed at 12 weeks, or at the end of the period of contra-indication to heparin. The alpha risk will be of 5% bilaterally.

Concerning the analysis of secondary endpoints, the same approach as above will be used for categorical variables. For quantitative variables, we also deem a treatment effect, period and order using a mixed model in which the subject will be returned as a random effect and to take into account the repeated nature of the data.

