**4- Experimental plan**

***Choice of the experimental plan and justification***

It is a single-center, randomized, open-type N-of-1 trial (cross-over test series randomized in unique individuals). This is an open study since the techniques cannot be blinded ; however the endpoint chosen is objective (clotting or non-clotting of the dialysis circuit), and not amenable to interpretation. Moreover, the patient is not necessary blinded because this should not influence the response. The choice of N of 1 trial is justified because it is important to choose the best technique according to the patient, and the experimental design can provide an individual response and assess the repeatability of the response by the same technique in the same patient. This experimental design is made possible due to the completion of three dialysis sessions per week chronically ineffective a dialysis session to the next session with a rapid assessment (the same day as the dialysis session) of the test main judgment and fact will be selected patients with contra-indication for LMWH for at least 3 consecutive dialysis sessions without heparin. In addition, this experimental design allows techniques comparison across treatment groups.

The unit of randomization will be patient and will be made according to the following scheme:

- A = discontinuous rinses, B = dilution and C = adsorbed heparin
- The 6 possibles sequences of treatments are:
  - ABC
  - ACB
  - BAC
  - BCA
  - CAB
  - CBA

The patient will be randomized into one of six arms and make sure to have a number of patients included multiple of 6 (see calculation of the number of subjects required). Randomization will be by random blocks of varying size. The order of the types of sessions vary all three triplets for the same patient if the dialysis without heparin must be repeated beyond the first triplets. As a patient may contribute to several sequences, the patient will be considered as a cluster randomization.

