**8- Data management and statistics**

***Justification of the number of patients to include***

The calculation of the number of subjects to include derives from the MacNemar test comparing groupes paired for a binary criteria:

|  | Response to treatment B | | | |
| --- | --- | --- | --- | --- |
| Response to the traitement of reference | Failure | Success | Total | Anticipated  Proportion |
| Failure | *r* | *s* | *r+s* | 1 - |
| Success | *t* | *u* | *t+u* |  |
| Total | *r+t* | *s+t* | Npaires |  |
| Anticipated  Proportion | 1 - |  |  |  |

This calculation is based on the estimation that =s/t measures the degree by which a patient will have a success with the reference treatement and a failure with treatment B, compared to failure with the reference treatement and success with treatment B. Of note, patients (*r+u*) having success-success or failure- failure are not taking into account in this calculation. The latter is based on anticipation of marginal probabilities of success, et , defined by the absence of circuit coagulation with each treatement:

- null hypothesis  : 70% in the reference treatment group (30% of clotting), group A,
- = 80% in the dilution group (20% of clotting), groupe B,
- = 90% int the AN 69 ST membrane (10% of clotting), group C,

thus estimating the proportion of discordant pairs :discordant = (*s+t*)/Npairs as well as values

Accoring to published tables, sample size tables for clinical studies, Blackwell Science, 1997 :

- number of pais
- to compare A and B with alpha=5% an a power of at least 80 %, values are for discordant = 0.38 et = 1,7, i.e 294 pairs of dialysis sessions.
- to compare A and C with alpha=5% and a power of 80 %, values are fordiscordant = 0.34 et = 3,85, i.e 65 pairs of dialysis sessions.
- In sum, at least 294 triplets of dialysis sessions are needed, i.e. 882 dialysis sessions, corresponding to 65 patients to recruit over 12 months.
- Each patient being a cluster of dialysis sessions patient, the number of dialysis sessions has to be increased according ta an inflation coefficient based on putative intra-class correlation ( 0.001 to 0.01) ; the inflation coefficient is estimated to range from 1,002 to 1,5 for a mean cluster of 6 dialysis sessions, i.e a raise from 884 sessions to 1323. We finally estimate the need to perform 1050 dialysis sessions in 75 different patients.

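### As worded, the subject-specific and mixed models carry only a patient-level term, so if technique effects differ between patients their standard errors for the average effects are too small

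*Protocol*

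**What the plan says.** **Pooled analysis of clotting** (protocol section 8, Main Analysis). Two approaches are listed without ranking. The first is "a marginal model estimating the effet of treatments taking into account other covariates (order effect or group effect, the Generalized Estimating Equations"; its variance estimator is not stated. The second is "a subject-specific model using a latent variable taking into account independent responses for a given subject". Both are referred to a methods paper on binary crossover data, and no model equation is written out.

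**Secondary endpoints** (the paragraph that follows). Categorical endpoints follow the same approach. Quantitative endpoints are analysed "using a mixed model in which the subject will be returned as a random effect", with treatment, period and order effects. No second model is named for them.

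**Reason for the design** (section 4, Choice of the experimental plan and justification). The N-of-1 format is chosen because "it is important to choose the best technique according to the patient" and because the repeatability of a technique within a patient can be assessed. For randomisation, "the patient will be considered as a cluster randomization".

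**Individual analysis** (Main Analysis). Patients with at least 18 sessions get their own Fisher tests of A vs B and A vs C.

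**The concern.** A single patient term says that some patients clot more than others, by the same amount under every technique. It does not allow rinsing to work well in one patient and badly in another. Yet the design rationale, the individual Fisher tests and the rule in Stopping rules that drops a technique for a patient after three consecutive failures all treat that as possible.

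If it happens, sessions of one technique in one patient resemble each other more than the patient term explains. A model that takes responses as independent given the patient then treats the tenth triplet of a long-stay patient as being as informative about the average effect as the first triplet of a new patient. A few long-stay patients who happen to do well on one technique can then produce a significant average effect.

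**Working it through.** **1. The plan's own figures.** With 70% and 80% success and independence within pairs, the discordant share is 0.30×0.80 + 0.70×0.20 = 0.38 and the ratio is 0.24/0.14 = 1.714. The two-sided McNemar formula at 5% and 80% power gives 296 pairs (Connor) or 293 (Miettinen), against 294 stated. For A vs C, 0.27 + 0.07 = 0.34 and 0.27/0.07 = 3.857 give 65 (Connor), as stated. These counts do not depend on the models questioned here.

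**2. What the plan says about correlation.** The stated ICC is 0.001 to 0.01, with an inflation coefficient of 1.002 to 1.5 at a mean cluster of 6. The usual formula 1 + (m−1)×ICC gives 1 + 5×0.01 = 1.05 at the upper ICC. A coefficient of 1.5 needs ICC = 0.5/5 = 0.10. The plan did use 1.5: 882×1.5 = 1323, its upper session count. Neither ICC is a variance of technique effects between patients, and the protocol gives none.

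**3. Assumed session mix.** 75 patients. 60% (45) have 1-2 triplets, as in Main Analysis. 40% (30) have 6-12 triplets, from the 18-session threshold to the 12-triplet maximum in Duration of participation. That every long-stay patient reaches 6 triplets is an assumption.
- Triplets: 45×1.5 + 30×9 = 67.5 + 270 = 337.5, or about 1,010 sessions against 1,050 planned.
- Share from long-stay patients: 270/337.5 = 80%.
- Sum of squared triplet counts: 45×2.5 + 30×85 = 2662.5.
- k = 2662.5/337.5 = 7.9. This is the effective number of triplets per patient over which a patient-specific technique effect is repeated.

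**4. Quantitative endpoints.** Let s be the patient-by-technique share of total within-patient variance. The true variance of an average contrast, divided by the variance that the patient-only model reports, is approximately (1−s) + s×k. The type I error of a nominal 5% test is then 2×[1 − Φ(1.96/√ratio)].

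| s | ratio | type I, formula | type I, simulated |
|---|---|---|---|
| 1% | 0.99 + 0.079 = 1.07 | 5.8% | 5.3-5.6% |
| 5% | 0.95 + 0.394 = 1.34 | 9.1% | 8.9-9.1% |
| 10% | 0.90 + 0.789 = 1.69 | 13.2% | 12.8-13.8% |
| 20% | 0.80 + 1.578 = 2.38 | 20.4% | 21-22% |

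At s = 0 the simulated error is 4.6-4.9%, so the model is correct when patients do not differ. Patient-clustered standard errors stay at 5.0-5.9%.

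**5. Clotting.** The simulation had 30% clotting under every technique, 1,500 trials per row, and a logistic model with a patient intercept only. The ICC was put on the logit scale as variance v = ICC/(0.3×0.7). The SD of the patient-specific log odds ratio is √(2v) if all of v is technique-specific and √v if half of it is.

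| ICC | technique-specific part | SD of log OR | reported SE / true SD | type I |
|---|---|---|---|---|
| 0.01 | half | 0.22 | 0.98 | 5-6% |
| 0.01 | all | 0.31 | 0.94-0.99 | 6-7% |
| 0.10 | half | 0.69 | 0.84-0.86 | 9% |
| 0.10 | all | 0.98 | 0.78-0.79 | 12% |

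In the 0.10 rows, coverage of the 95% interval is about 91% and 88%. The GEE with a patient-clustered sandwich variance stays at 4.5-6% in all four rows.

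**The case against.** **The wording is brief.** No equation is given, the sentence on the latent variable is a damaged translation, and an SAP could add a term. This stands as a caution: the point is about the text as worded. But conditional independence given the subject is a stated modelling assumption, and the mixed-model sentence names one random effect. A statistician who followed the text would fit the models examined here.

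**A reader might infer that the intervals are too narrow as a matter of fact.** The documents do not support that. The protocol gives no heterogeneity variance, and at its stated ICC ceiling the shortfall for clotting is about 1-6% of the standard error. The larger clotting figures rest on an ICC of 0.10, which comes from an inflation coefficient that does not agree with the stated ICC.

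**A reader might infer that the primary analysis as a whole is unsound.** It is not. The GEE is listed first, the patient is the declared cluster, and the same approach carries over to categorical secondary endpoints. With a sandwich variance these are protected, although that variance is not named.

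**A reader might infer that individual response is left unanswered.** It is not. The Fisher tests address it patient by patient, and section 4 gives reasons to look for individual differences without asserting that they exist.

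**A test of no difference in any patient is valid with a patient term alone.** This is correct. The difficulty arises when the result is read as an average effect across patients who may differ.

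**The simulation is simplified.** Some long-stay patients may leave at the 18-session analysis or have a technique dropped, and either would change the mix.

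**Conclusion.** The point holds in conditional form. The exposure lies in two places: the companion subject-specific model for categorical endpoints, and the only model planned for quantitative endpoints such as urea dialysance. If technique effects differ between patients, the model-based standard errors there are too small, mainly because a minority of patients supplies about 80% of the triplets under the assumed mix.

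The size cannot be read from the protocol. For clotting it ranges from minor at the stated ICC to roughly a doubling of the false-positive rate at the ICC implied by the 1.5 coefficient. For quantitative endpoints the stated ICC is no guide, because it concerns clotting, and a technique-specific share of 5% of within-patient variance is enough to bring the error to about 9%. Confidence is medium: the mechanism is certain, the size is assumed. The change is worth making because it costs little and removes the dependence on an unknown variance.

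**What to change.** In section 8, Main Analysis and the paragraph on secondary endpoints:

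- Base inference on average technique effects on patient-clustered robust standard errors. For clotting, name the GEE with a sandwich variance as that analysis.
- Alternatively, add a patient-by-technique random effect to the subject-specific model and to the mixed model, with robust standard errors as the stated fallback if the model does not converge.
- Where the term is fitted, report the estimated patient-by-technique variance with its interval, as a supplement to the individual Fisher analyses.

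Cost: one variance term or one option in models already planned, with no extra patients or data. Intervals widen somewhat if patients differ and hardly at all if they do not.

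### Eighteen sessions do not give the individual Fisher analysis sufficient power: at the plan's own clotting rates it has about 4.2% for A vs C and 2.5% for A vs B

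*Protocol*

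**What the plan says.** The protocol analyses its main criterion at two levels, by treatment group and by individual (section 8, Main Analysis). The individual level is for the 25 to 30 patients expected to have a prolonged contra-indication, and it begins "after at least 18 sessions to warrant sufficient power". The failure percentages are compared for "technique A vs B, and also technique A vs C". On the test, the plan says: "The exact Fisher test in this setting may be viewed as a randomisation test". On pairing: "Appairment will not be taken into account". On the level: "Significativity threshold will be of 10% for a bilateral test".

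The result decides whether the patient stays: "if one or several techniques are efficient, the patient will end the study". If no technique looks superior, the patient may go on for at least one more triplet. A further analysis follows at 12 weeks or when the contra-indication ends, and the paragraph closes: "The alpha risk will be of 5% bilaterally".

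Three other places bear on this. Section 4 (Duration of participation) caps a patient at 12 triplets. Section 8 (Stopping rules) takes a technique out of a patient's randomisation after three failures in a row. Section 4 (Choice of the experimental plan) says of the allocation: "The order of the types of sessions vary all three triplets for the same patient". The only anticipated clotting rates are the 30%, 20% and 10% in the sample-size section. No power figure and no effect size are given for the individual analysis.

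**The concern.** The sample-size section asks for 294 pairs of sessions to separate 30% from 20% clotting, and 65 pairs to separate 30% from 10%. That is a McNemar calculation at 5%, so it is not the same test, but the scale is telling. The individual analysis compares the same techniques with 6 sessions each and calls the power sufficient.

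Section 4 justifies the N-of-1 design by the need to find the best technique for each patient, and a study-exit rule depends on the individual verdict. If the power claim is wrong, nearly every individual analysis will end without a verdict even when the techniques differ as the plan expects. Readers of the protocol would also be misinformed about what those analyses can show.

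**Working it through.** **1. Check that the rates are read correctly.** The plan has no individual power figure to reproduce, so I reproduced its group-level figures. With discordant proportion d and ratio ψ, the number of pairs is N = [1.96(ψ+1) + 0.842√((ψ+1)² − (ψ−1)²d)]² / [(ψ−1)²d].

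- A vs C: d = 0.3×0.9 + 0.7×0.1 = 0.34. With the stated ψ of 3.85, N = 64.4, so 65, as stated.
- A vs B: d = 0.3×0.8 + 0.7×0.2 = 0.38, ψ = 0.24/0.14 = 1.714. N = 296 against the stated 294. The rounded ratio 1.7 gives 305.

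The rates 30%, 20% and 10% are therefore the ones the plan works with.

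**2. Inputs for the individual test.** Each triplet contains each technique once, so 18 sessions are 18/3 = 6 per technique. The test is unpaired Fisher, two-sided, level 10%. Sessions are taken as independent, as the plan assumes, with a constant rate per technique within the patient. The dropping rule is left out here.

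**3. Which results are significant at 6 vs 6.**

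- 3/6 vs 0/6: p = 2×20/220 = 0.18, not significant.
- 4/6 vs 0/6: p = 2×15/495 = 0.061.
- 5/6 vs 1/6: p = 2×(36+1)/924 = 0.080.
- 6/6 vs 2/6: p = 0.061.

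At least 4 failures in 6 on one technique are needed. At a 30% rate, the binomial probabilities of 4, 5 and 6 failures are 0.0595, 0.0102 and 0.0007.

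**4. Power at 18 sessions.**

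- A vs C, right direction. At 10%, C has 0 failures with probability 0.5314, at most 1 with 0.8857, at most 2 with 0.9841. Sum: 0.0595×0.5314 + 0.0102×0.8857 + 0.0007×0.9841 = 0.0414. The wrong direction adds 0.0002. Total 4.2%.
- A vs B, right direction. At 20%, the same three probabilities are 0.2621, 0.6554 and 0.9011. Sum: 0.0595×0.2621 + 0.0102×0.6554 + 0.0007×0.9011 = 0.0230. The wrong direction adds 0.0025. Total 2.5%.
- Both techniques at 30%: the test rejects 2.4% of the time, half in each direction.

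**5. At the cap, and what 80% would need** (same exact enumeration).

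| Sessions per technique | Two-sided level | A vs C | A vs B |
|---|---|---|---|
| 6 | 10% | 4.2% | 2.5% |
| 12 (cap) | 5% | 9.5% | 3.1% |
| 12 (cap) | 10% | 19.8% | 7.8% |
| 56 | 10% | 80% | – |

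**6. More generous readings.** A one-sided 10% test at 6 vs 6 gives 14.0% and 7.2%. Reading the 18 as sessions per technique, which exceeds the cap, gives 29% and 9.7% at two-sided 10%.

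**7. Larger individual contrasts at 6 vs 6, two-sided 10%.** 60% vs 10% gives 38%, 80% vs 10% gives 74%, and 90% vs 10% gives 89%.

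**The case against.** The strongest defence is that an N-of-1 analysis may be meant for patients with large contrasts of their own, for whom group averages are the wrong yardstick. An 80% vs 10% contrast would be found with 74% power. This stands as a limit on the finding, but the protocol names no such contrast, and 60% vs 10% already falls to 38%.

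It is also fair that the consequences are limited. The chance of any significant verdict at 18 sessions is 5.2% at the planned rates. Among 25 to 30 patients that is 25×0.052 = 1.3 to 30×0.052 = 1.6 exits, each after at least 18 sessions contributed to the global analysis.

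A reader might infer more than the document supports:

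- **That the verdicts are mere noise.** The 5.2% compares with 4.4% when all three rates are 30%, but those figures pool two comparisons and both directions. For A vs C in the right direction it is 4.1% against 1.2%. The test is weak, not uninformative.
- **That the three-failures rule cuts power further, to 1.8% and 0.9%.** Those values count only patients who reach 6 sessions on every technique. The plan requires 18 sessions in total and does not discard data from a dropped technique: 3/3 vs 0/6 gives p = 0.012. Keeping all data, simulation gives about 7.2% and 4.6% in the right direction. The effect changes sign with a choice the plan leaves open.
- **That a 10% look followed by a 5% look inflates error.** With all rates at 30% and the dropping rule set aside, simulating both looks and both comparisons gives 6.4% overall, below 10%. What is unclear is which analysis each level governs.
- **That Fisher's test is invalid because few allocations were possible.** A literal reading of the sentence on order gives 6×6 = 36 allocations against 924 splits. That sentence is an unclear translation. Even a new order for every triplet allows only 2^6 = 64 A/C swaps, and the gap comes from ignoring pairing, which the plan discloses.
- **That non-significance will be taken as no difference.** The plan says only that the patient may continue.

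**Conclusion.** The finding holds as one of low and misstated power, confined to the individual analysis. Against a claim of sufficient power, the plan's own test, level and rates give 4.2% and 2.5% at 18 sessions, and no more than 19.8% and 7.8% at the cap. The easier comparison would need about 56 sessions per technique where at most 12 are possible.

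This rests on applying the group clotting rates within each patient, on independent sessions, and on 6 sessions per technique. It does not show excess false positives. The sample size and the group-level analysis do not depend on it.

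**What to change.** - In section 8 (Main Analysis), delete the statement that 18 sessions give sufficient power. State the figures above and the assumption behind them.
- Report each patient's failure rates and technique differences with intervals, labelled descriptive. One route is the subject-specific model already planned, with a patient-by-technique effect added. Say that a non-significant test is not evidence of no difference in that patient.
- Reconcile the exit rule in Main Analysis with this low power and with the three-consecutive-failures rule in Stopping rules. Say how sessions on a dropped technique enter the test.
- State which analysis the 10% and the 5% levels apply to.
- In section 4, state how often the order is re-randomised within a patient.

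The cost is a few sentences of text. What is lost is a per-patient p-value that had little power.

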***Study exit***

The inclusion of a patient in the research protocol will end

• in case of premature termination (before three successive sessions are conducted)

• at the end of the maximum period of scheduled follow-up (3 months)

• withdrawal of patient’s consent (at any time)

• in case of permanent change of dialysis center

• in case of death

• in case of a technical superiority in the interim statistical analysis (see page 14)

Patients will be supported by the usual care practices in each dialysis center.

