***Stopping rules***

If three consecutive failures to the same technique, randomization will continue on the remaining 2 techniques if the patient needs to continue its sessions without systemic heparin and if 3 months of inclusion are not met.

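### The two-look individual analysis limits the number of looks but does not control error, and a technique withdrawn after three failures can roughly double the false-verdict rate if it stays in the Fisher test

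*Protocol*

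**What the plan says.** All references are to the protocol; no separate SAP is shown.

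- **First look** (section 8, Main Analysis). Patients with a prolonged contraindication, projected at 25 to 30, are analysed individually "after at least 18 sessions to warrant sufficient power". Two comparisons are made: "The percentage of technical failures (technique A vs B, and also technique A vs C) will be performed". The test is unpaired: "The exact Fisher test in this setting may be viewed as a randomisation test". The sessions are said to be statistically independent. "Significativity threshold will be of 10% for a bilateral test", and a reason is given for that choice.
- **Exit.** "if one or several techniques are efficient, the patient will end the study". Section 5, Study exit, also lists superiority at the interim analysis as a ground for ending participation.
- **Second look.** The remaining patients may continue for one or more triplets. Then: "To avoid multiple analysis and alpha risk, a new analysis will be performed at 12 weeks", or when the contraindication ends. A separate sentence sets alpha at two-sided 5%.
- **Withdrawal of a technique** (section 8, Stopping rules). "If three consecutive failures to the same technique" occur, randomisation goes on with the other two. The paragraph does not say how the withdrawn technique enters the individual test.
- **Maximum data** (section 4, Duration of participation). Three months or 12 triplets, so 36 sessions.

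**The concern.** A second analysis is itself a multiple analysis. It can only add false verdicts to those already made at the first look, and patients declared positive at 10% never face the 5% test. No allowance is stated for two looks or for two comparisons.

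The withdrawal rule raises a separate difficulty. Fisher's test is justified here as a randomisation test on independent sessions. Once a technique is stopped because of its results, its number of sessions depends on its outcomes. Its record necessarily ends on three failures, while the other two keep accruing and can return to their average.

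The individual analysis is one of the two analyses planned for the main criterion, and section 4 justifies the N-of-1 design by the wish to choose the best technique for each patient. An exit verdict will be read as an established result for that patient, so its error rate should be known.

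**Working it through.** **Inputs.** 18 sessions at look 1, so 6 per technique if none is withdrawn; A vs B and A vs C; Fisher two-sided at 10%, then 5% (Main Analysis). 36 sessions at look 2, so 12 per technique (Duration of participation). Assumption: all three techniques share one clotting risk, centrally 30%, the protocol's reference rate (Justification of the number of patients), with a range of 10% to 50%. Sessions are independent, as the protocol states. The protocol gives no overall per-patient error, so there is only the nominal 10% and 5% to compare with.

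**Step 1: real size of one first-look test.** With 6 vs 6, Fisher reaches p ≤ 0.10 only from 0 vs 4 (p = 0.061), 1 vs 5 (0.080) or 2 vs 6 (0.061) failures; 0 vs 3 gives 0.18 and 1 vs 4 gives 0.24. At 30% clotting, for Binomial(6, 0.3): P(0) = 0.1176, P(1) = 0.3025, P(2) = 0.3241, P(≥4) = 0.0704, P(≥5) = 0.0109, P(6) = 0.0007.

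Size = 2 × (0.1176 × 0.0704 + 0.3025 × 0.0109 + 0.3241 × 0.0007) ≈ 2.4%.

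The nominal 10% is far from reached because the test is discrete.

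**Step 2: two comparisons, two looks, no withdrawal (exact enumeration).** Look 2 uses cumulative data from patients who have not exited.

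| Common clotting risk | Look 1 | Added at look 2 | Any false verdict |
|---|---|---|---|
| 10% | 0.2% | 0.4% | 0.6% |
| 20% | 1.9% | 1.8% | 3.6% |
| 30% | 4.4% | 2.2% | 6.5% |
| 40% | 6.4% | 2.4% | 8.7% |
| 50% | 7.1% | 2.5% | 9.6% |

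(Rows may differ by 0.1 from rounding.)

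**Step 3: why a withdrawn technique matters.** Suppose rinses clot three times out of three and are withdrawn. By session 18 the other two share 18 − 3 = 15 sessions, 7 and 8.

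- 3/3 vs 1/7: p = C(4,3)/C(10,3) = 4/120 = 0.033.
- 3/3 vs 2/8: p = C(5,3)/C(11,3) = 10/165 = 0.061.

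Both pass at 10%. At 30% clotting, P(≤1 of 7) = 0.329 and P(≤2 of 8) = 0.552. The chance of at least one false verdict is 1 − 0.671 × 0.448 ≈ 70%, ignoring any second withdrawal. Three failures in a row therefore largely decide the test.

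**Step 4: full design with withdrawal (simulation, 40,000 to 80,000 patients per setting).** The withdrawn technique is kept in the test with its frozen record.

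| Common clotting risk | Look 1 | Any false verdict |
|---|---|---|
| 20% | about 4.6% | about 8% |
| 30% | 9.3% to 9.5% | about 14% |
| 40% | about 11% | about 15% |

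At 30%, the total runs from 12.1% to 14.1% according to how the interrupted triplet and a second withdrawal are handled. The rule fires by session 18 in about 23% of patients. Of these, about 37% get a false first-look verdict, against about 1.2% where it did not fire. Check: 0.23 × 0.37 + 0.77 × 0.012 ≈ 9.4%.

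**Step 5: which cause is larger.** With withdrawal in force at 30%, a single final test at 5% with no first look still gives 9.2%. Without withdrawal the same single test gives 3.2%.

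**Step 6: closing the affected comparisons.** If no test is made on a comparison that involves a withdrawn technique, the rate at 30% is about 2% to 2.5% (about 2% at 20%, 2.5% at 40%).

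**The case against.** - **The quoted phrase may concern only the timing of looks.** It follows the statement that a patient may continue for one or more triplets, so it can mean that patients are not retested after each one. This stands in part. At 30% without withdrawal, a 5% test after every triplet gives 7.9% and a 10% test 15.1%, against 6.5% for two looks. Fewer looks do help, but they limit multiplicity rather than avoid it.
- **The protocol nowhere promises 5% over both looks.** This stands. The 5% is attached to the second analysis, and the 10% is declared and justified. A reader might infer a broken promise of 5% overall; the text does not go that far.
- **A reader might infer that the 10%-then-5% sequence by itself gives about 14%.** It does not. The looks alone stay below 10% at every risk tried. The product 1 − 0.90 × 0.95 = 14.5% lands near the same figure by coincidence: it ignores the discreteness of Fisher's test, the correlation between the looks and the second comparison.
- **A reader might infer that no second threshold could bring the error to 5%, because the first is looser.** This is also wrong for the looks alone: look 1 spends 4.4% at 30%, so a strict enough second look would hold 5% there.
- **The 14% depends on a handling rule that the protocol does not state.** This stands and is the main limit. The Stopping rules paragraph speaks only of randomisation, and a SAP may settle the analysis. But the Main Analysis makes no exception for withdrawn techniques, so keeping them in the test is a natural reading of what is written.

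**Conclusion.** The point holds in limited form. The two-look scheme does not control the per-patient error over two looks and two comparisons. With equal techniques at 30% clotting, 6.5% of patients get a false verdict from the looks alone (0.6% to 9.6% for risks of 10% to 50%), above 5% and below the declared 10%. The larger problem is outcome-dependent withdrawal. If the withdrawn technique stays in the Fisher test, the rate is about 14% at 30% (about 8% at 20%, 15% at 40%), and the randomisation-test and independence arguments no longer apply.

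Among 25 to 30 individually analysed patients with equal techniques at 30%, this means about 2 false verdicts from the looks alone (25 to 30 × 0.065 = 1.6 to 2.0) or about 3 to 4 with withdrawal (25 to 30 × 0.136 = 3.4 to 4.1).

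The figures assume equal risk, independent sessions and 36 sessions for every patient who has not exited. Earlier ends of the contraindication shrink the second-look part but leave look 1 as it is. The calculation concerns the individual verdicts; it does not show that the group-level analysis is wrong.

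**What to change.** In section 8, Main Analysis:

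1. Replace the wording that the 12-week analysis avoids alpha risk with a statement that it limits the number of looks. Give the per-patient error over both looks and both comparisons with its assumptions: about 6.5% at 30% clotting without withdrawal, and about 14% if withdrawn techniques stay in the test.
2. Label each exit verdict as made at the 10% look.
3. State that superiority is not declared by Fisher's test from a comparison that involves a technique withdrawn under the Stopping rules. Report such comparisons separately, as descriptive. This is what brings the rate down to about 2% to 2.5% at 30%.

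The cost is wording, a short simulation, and fewer formal verdicts: by session 18 at 30% clotting, about 23% of patients would have a withdrawn technique. No sessions, patients or procedures are added, and the clinical rule on withdrawing a technique is unchanged.
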